### Peripheral artery disease/foot ulcer:

1) Patients with critical ischemia (including: resting pain, ischemic ulcers, or gangrenous ulcers) will be referred to the outpatient clinic of vascular surgery (32, 37).

2) Patients with or without symptoms of intermittent claudicatio and ABI>1,4 will be referred to examination with toe-brachial index (TBI) at the department of Endocrinology. If TBI is abnormal, patients will be diagnosed with lower extremity artery disease (LEAD), and treatment with ASA and high dose statins therapy will be initiated. Target LDL level <1.4 mmol/L (32, 37).

3) Patients with or without symptoms of intermittent claudicatio and ABI<0.9 are diagnosed with lower extremity artery disease (LEAD), and treatment with ASA and high dose statins therapy will be initiated. Target LDL level <1.4 mmol/L (32, 37).

4) Patients with diabetic foot ulcers will be referred to the outpatient clinic for wounds (32, 37).

5) Patients with abnormal monofilament test and symptoms of neuropathy will be referred to the department of endocrinology (32).

- Vaccinations:
  Anamnesis regarding vaccination status is obtained, and recommendations of yearly influenza vaccination (38). COVID vaccinations (39) after current local guidelines.

Examinations
1) Blood samples will be drawn at the baseline visit and at the three years follow-up visit. Approximately 80 ml of blood will be collected. Blood samples will be analyzed for; Hematology: Hemoglobin and leucocytes.
Lipid profiles: Total cholesterol, high-density lipoprotein (HDL), low-density lipoprotein (LDL), and triglycerides. Diabetes status: Glycated haemoglobin (HbA1c). Liver function: Alanine transaminase (ALAT), alkaline phosphatase, and gamma-glutamyl transferase (GGT), lactate dehydrogenase (LDH), and FIB-4 index for liver fibrosis assessment. Cardiac markers: N-terminal-pro b-type natriuretic peptide (NT-proBNP) and troponin T. Electrolytes: Sodium and potassium. Renal function: Creatinine and estimated glomerular filtration rate. Inflammatory marker: C-reactive protein (CRP).

2) Urine samples will be collected at the baseline visit and at the 3 year follow-up visit and albuminuria will be evaluated. This will include measurement of urine albumin and creatinine to calculate the albumin creatinine ratio (UACR) from a spot urine sample.

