3) Blood pressure measurement: Blood pressure will be measured at baseline and at the 3 year follow-up visit. If blood pressure is above 130/80 mmHg after 10 minutes the CMC group will measure blood pressure at home (3 times daily for 3 days) and be treated according to the Cardio-metabolic treatment algorithm. Patients in the control group will be advised to contact the general practitioner (GP) in case of blood pressure above 130/80 mmHg.

4) Ankle-brachial index (ABI): ABI will be assessed at the baseline visit and at the 3 year follow-up visit. During the procedure, patients will be instructed to lie down in a supine position and rest for a period of 10 minutes. Blood pressure measurements will be performed in both the brachial arteries and the dorsalis pedis arteries using a blood pressure cuff and a Doppler ultrasound devise. ABI will hereby be calculated.

5) Monofilament test: will be performed at the baseline visit and at the 3 year follow-up visit. This test involves applying a 10-g monofilament at the distal plantar aspect of both great toes and metatarsal joints to assess pressure sensation.

5) Transient Elastography (Fibro-scan): Patients will be evaluated for liver fibrosis using serological test with FIB-4 at baseline and at 3 year follow-up visit. Patients with high risk (FIB-4: > 2,67) or moderate risk (FIB-4: 1.3 - 2.67) at baseline and at 3 year follow-up will be referred to the department of gastroenterology for a fibro-scan. In case of suspicion of fibrosis or cirrhosis an individual risk assessment will be made by a hepatologist.

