## Follow-up visits

**Individual visits:**If a new treatment is prescribed that causes need for further monitoring or evaluation, individual visits as either telephone consultations or attendances will be arranged. In some cases, additional blood samples, urine samples will be collected and evaluated. Efforts will be made to keep participants on study intervention until they are completed in the CMC intervention.

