| To compare the occurrence of microvascular complication, nephropathy, in patients receiving optimal diabetes care in a Cardio-Metabolic Clinic versus usual care | - Change in urinary albumin-to-creatinine ratio (UACR) |
| Units of measure: Measured in ratio to baseline. | Time Frame: From baseline to 3 years of FU. |
| To compare the occurrence of microvascular complication, nephropathy, in patients receiving optimal diabetes care in a Cardio-Metabolic Clinic versus usual care | - Change in Chronic Kidney Disease (CKD) stage   Calculated by eGFR and albuminuria. |
| Units of measure: Measured in ratio to baseline. | Time Frame: From baseline to 3 years of FU. |
| To compare the occurrence of microvascular complication, nephropathy, in patients receiving optimal diabetes care in a Cardio-Metabolic Clinic versus usual care | Time to first occurrence of a composite CKD endpoint consisting of:   - a decline in eGFR of more than 50%, - onset of end-stage kidney disease (dialysis, eGFR<15, kidney transplantation) - death from renal or CV causes |
| Units of measure: Measured in count of events. | Time Frame: From baseline to 3 years of FU. |
| To compare the occurrence of microvascular complication, liver fibrosis, in patients receiving optimal diabetes care in a Cardio-Metabolic Clinic versus usual care | - Change in fibrosis-4 (FIB-4).   FIB-4 is calculated using age, aspartate aminotransferase (ASAT), alanine aminotransferase (ALAT), and platelet count. |
| Units of measure: Measured in ratio to baseline. | Time Frame: From baseline to 3 years of FU. |
| To compare the occurrence of microvascular complication, liver fibrosis, in in high-risk patients receiving optimal diabetes care in a Cardio-Metabolic Clinic versus usual care | - Change in degree of liver fibrosis through a Fibro-scan |
| Units of measure: Measured in count of events. | Time Frame: From baseline to 3 years of FU. |

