| To compare the occurrence of macrovascular complications, peripheral artery disease (PAD) and/or ischemic heart disease (IHD), in patients receiving optimal diabetes care in a Cardio-Metabolic Clinic versus usual care | Time to first occurrence of a composite macrovasucular endpoint comprising:   - new diagnosis of lower extremity arterial disease (LEAD), - new/progression of foot ulcers, - surgical procedures related to PAD - coronary revascularization   Surgical procedures includes: percutaneous transluminal angioplasty, peripheral artery bypass, thrombectomy, thrombolysis, amputations.  Coronary revascularization includes: percutaneous coronary intervention (PCI), coronary artery bypass graft. |
| Units of measure: Measured in count of events. | Time Frame: From baseline to 3 years of FU. |
| To compare the occurrence of macrovascular complications in the lower extremities, in patients receiving optimal diabetes care in a Cardio-Metabolic Clinic versus usual care | - Change in ankle-brachial pressure index (ABI) |
| Units of measure: Measured in ratio to baseline. | Time Frame: From baseline to 3 years of FU. |
| To compare change in protocol-driven medication in patients receiving optimal diabetes care in a Cardio-Metabolic Clinic versus usual care | Change in protocol-driven medication:   - Lipid lowering medication - Antihypertensive medication - Anti-thrombotic medication - Anti-diabetic medication - Nephro-protective medication |
| Units of measure: Measured in percentage [%]. | Time Frame: From baseline to 3 years of FU. |
| To compare change in patient experienced symptoms in patients receiving optimal diabetes care in a Cardio-Metabolic Clinic versus usual care | - Change in symptoms as reported by patients using the Kansas City Cardiomyopathy Questionnaire (KCCQ) |
| Units of measure: Measured in score points (change in percentage [%]). | Time Frame: From baseline to 3 years of FU. |
| To compare the net cost of implementing a Cardio-Metabolic Clinic in patients receiving optimal diabetes care versus usual care | - Net cost of a Cardio-Metabolic Clinic:  Cost of Cardio-Metabolic Clinic minus averted costs   Averted costs includes: averted admissions, medical treatment, and productivity). |
| Units of measure: Measured in dollars [$]. | Time frame: From baseline to 5 + 10 years of FU. |

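### New LEAD in the macrovascular composite has no arm-neutral definition: the diagnosis rules sit in the clinic's algorithm, and LEAD already present at baseline is not excluded

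*Protocol*

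**What the plan says.** - **Endpoint.** The Outcomes table of the protocol lists "Time to first occurrence of a composite macrovasucular endpoint comprising" four components. One is "new diagnosis of lower extremity arterial disease (LEAD"). The others are new or worsening foot ulcers, PAD procedures and coronary revascularisation. The window is "Time Frame: From baseline to 3 years of FU". *New* is not defined, no ABI criterion is attached, and nothing is said about LEAD present at baseline.
- **Diagnosis rule.** The treatment algorithm, under Peripheral artery disease/foot ulcer, states: "Patients with or without symptoms of intermittent claudicatio and ABI<0.9 are diagnosed with lower extremity artery disease (LEAD"). For stiff vessels, "ABI>1,4 will be referred to examination with toe-brachial index (TBI"), and an abnormal TBI leads to the same diagnosis.
- **Who follows it.** The two sections on the clinic's organization and interventions activate the algorithm on randomization to the intervention arm and apply it to CMC participants.
- **Measurement.** Under Examinations, "ABI will be assessed at the baseline visit and at the 3 year follow-up visit". The Baseline visit section includes ABI for all participants, and the three-year visit repeats the baseline programme for everyone.
- **Controls.** Examinations tells control participants what to do about raised blood pressure. It gives no equivalent for an abnormal ABI.
- **Start of assessment.** The section on interventions in the clinic says that endpoint assessment starts only after the CMC intervention is complete, meaning full titration.
- **Kidney composite.** It includes "a decline in eGFR of more than 50" per cent. Blood samples are scheduled at baseline and year 3, but where new treatment needs monitoring, "In some cases, additional blood samples, urine samples will be collected and evaluated".

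**The concern.** The event is, in part, an act of the intervention. Take two participants with the same silent ABI of 0.8 at the baseline visit. In CMC the algorithm labels one as having LEAD soon after randomization, inside a window that opens at baseline. In the control arm the protocol records the other's number and attaches no diagnosis to it. That participant can score only through usual care or at the year-3 ABI, at the very end of the window. The trial is open label, so nothing else evens this out.

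A time-to-first-event comparison then partly measures when and by which rule disease was labelled, rather than whether the clinic prevented it. If the window opens at baseline, the error runs against the clinic and could hide a real benefit. If it opens only when the CMC intervention is complete, the early CMC labels may fall outside it while the same prevalent disease in controls counts at year 3. The error would then favour the clinic.

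**Working it through.** The protocol gives no figure for this composite, so there is none to reproduce. The check shows how far arm-dependent labelling alone can move the result when the clinic has no effect.

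**Inputs from the protocol:** 1500 participants randomized 2:1, so 1500 × 2/3 = 1000 CMC and 1500 × 1/3 = 500 control.

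**Assumed inputs (not in the documents):**
- *q*, the share with undiagnosed LEAD at baseline: 5%, 10%, 20%
- *r*, the true 3-year risk of the composite in both arms: 10%, 15%
- *f*, the share of control baseline cases scored by year 3: 0, 0.5, 1

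**Formulas, window read from baseline:**
- CMC risk = q + (1 − q)r
- Control risk = q[f + (1 − f)r] + (1 − q)r

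Example, q = 0.05, r = 0.10, f = 0: CMC = 0.05 + 0.95 × 0.10 = 0.145; control = 0.05 × 0.10 + 0.95 × 0.10 = 0.100; ratio = 1.45.

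Chance of a false significant difference (two-sided 0.05, normal approximation, pooled variance under the null), same example: pooled risk = (145 + 50)/1500 = 0.13; null SE = √(0.13 × 0.87 × (1/1000 + 1/500)) = 0.0184; alternative SE = √(0.145 × 0.855/1000 + 0.10 × 0.90/500) = 0.0174; Φ((0.045 − 1.96 × 0.0184)/0.0174) ≈ 0.70.

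| q | r | CMC risk | f = 0: control, RR, chance | f = 0.5: control, RR, chance | f = 1: RR |
|---|---|---|---|---|---|
| 5% | 10% | 14.5% | 10.0%, 1.45, 70% | 12.3%, 1.18, 22% | 1.0 |
| 5% | 15% | 19.3% | 15.0%, 1.28, 53% | 17.1%, 1.12, 16% | 1.0 |
| 10% | 10% | 19.0% | 10.0%, 1.90, >99% | 14.5%, 1.31, 58% | 1.0 |
| 10% | 15% | 23.5% | 15.0%, 1.57, 98% | 19.3%, 1.22, 46% | 1.0 |
| 20% | 10% | 28.0% | 10.0%, 2.80, >99% | 19.0%, 1.47, 97% | 1.0 |
| 20% | 15% | 32.0% | 15.0%, 2.13, >99% | 23.5%, 1.36, 93% | 1.0 |

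**Timing alone.** A Cox simulation (200 runs per q, r = 10%) scored CMC baseline cases at day 14. With control cases never scored, the median hazard ratios for q = 5%, 10% and 20% were 1.49, 1.99 and 3.02. With control cases scored at the 3-year visit they were 1.03, 1.06 and 1.13, and the share of runs with P < 0.05 was 3%, 3.5% and 20%. If controls are fully caught up at year 3, little bias remains except at high prevalence.

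**Other reading of the window.** Suppose early CMC diagnoses fall before assessment starts and all control baseline cases score at year 3. CMC risk is then about r and control risk is q + (1 − q)r, the mirror image of the f = 0 column. The ratio runs from 0.15/0.1925 = 0.78 (q = 5%, r = 15%) to 0.10/0.28 = 0.36 (q = 20%, r = 10%), now in favour of CMC. This is an extreme case, shown only because it fixes the direction.

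**The case against.** **A reader might infer that controls cannot score at all.** The documents do not support that. ABI is measured in every participant at baseline and at three years, the year-3 visit lies within the window, and usual care can make the diagnosis. The difference lies in timing and in the stated rule.

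**Scoring near day 0 is one reading, not a stated rule.** *New* can be taken to exclude anyone whose ABI was already abnormal at the common baseline visit, and the sentence on the start of endpoint assessment may exclude early CMC diagnoses. Operational event definitions often go into an analysis plan, which is not at hand. This has force. But the protocol itself fixes the component, the window, the arm-specific diagnosis rule and the conflicting start, and these do not fit together. Dropping early CMC diagnoses without treating control baseline cases alike would reverse the asymmetry, not remove it.

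**The large ratios are worst cases.** This stands. They need no control baseline case to be scored by year 3, and the prevalence and risk inputs are assumptions.

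**A reader might extend the point to the kidney composite with equal force.** The text does not bear that out. The extra samples are taken only in some cases, controls may have creatinine measured by their own doctors at an unstated frequency, and no size can be given. Death, dialysis and transplantation there, like procedures and revascularisation in the macrovascular composite, do not depend on a CMC diagnosis rule.

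**Conclusion.** The concern holds for one component of one secondary composite. As written, ascertainment of new LEAD depends on arm, because the only diagnosis rules belong to the CMC algorithm, *new* is undefined, and the protocol contradicts itself on when assessment begins.

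With the window read from baseline and the assumed inputs above, the spurious 3-year risk ratio lies between 1.0 and 2.8, against CMC. Where in that range depends almost entirely on how many control baseline cases are scored by year 3. With the window opening after completion of the intervention, the bias could favour CMC. The direction therefore cannot be stated until the two passages are reconciled, and a firm claim that the design penalises the clinic would go beyond the text.

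The primary MACE endpoint is not affected. The eGFR component is a lesser, unquantified instance of the same kind. The point should be corrected but does not threaten the trial's main conclusion.

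**What to change.** For the endpoint only, without touching care in either arm:

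1. Define new LEAD by one criterion in both arms: protocol ABI below 0.9 at follow-up in participants with baseline ABI of 0.9 or more and no prior LEAD.
2. Class participants who are positive at baseline as prevalent in both arms. Do not count diagnoses that rest on the baseline ABI or on the TBI step stated only for CMC.
3. State one rule, identical in both arms, for baseline ABI above 1.4.
4. Reconcile the sentence on the start of endpoint assessment with the window in the Outcomes table, so that both arms have the same time zero.
5. For the kidney composite, judge the eGFR decline from the scheduled 3-year sample in both arms, at least as a sensitivity analysis.

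Under the no-effect illustration, points 1 to 3 return the ratio to 1.0. There is no need to break either composite into separate binary and time-to-event parts.

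**Cost.** This is a change of endpoint wording; ABI and eGFR are already scheduled in both arms. LEAD found only by TBI no longer counts. Onset is known only to the year-3 visit. The component is missing for participants who die before that visit or do not attend it, and the analysis must say how they are handled.

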## Interventions – the Cardio-Metabolic Clinic

#### Organization in the Cardio-Metabolic clinic

The Cardio-metabolic clinic is based on a low-cost model and is organized in three different layers centered on the patient. The innermost layer consists of medical students or specialized cardio-metabolic nurses, who have the daily contact with the patients in the Cardio-metabolic Clinic. Patient´s medical history and data from the baseline visit are entered into the Electronic Case-Report Form (REDCap). When Patients are randomized to the intervention arm a decision-making algorithm in the REDCap-system will be activated ensuring that patients receive the most optimal and tailored medical treatment according to the latest guidelines and recommendations for diabetes management. The second layer consists of a cardiologist who the medical students or cardio-metabolic nurses will review the patients risk profile and algorithm-recommended treatment with. If the cardiologist needs further counselling for patient management, the third layer will be contacted. The third layer consists of an endocrinologist, a nephrologist and a hepatologist and this multidisciplinary collaboration will ensure the most optimal diabetes management in challenging cases.

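### The macrovascular composite scores a new LEAD diagnosis as an event, but the only written rule that makes this diagnosis from ABI or TBI belongs to the clinic arm, and new is not anchored to the baseline ABI

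*Protocol*

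**What the plan says.** All references are to the Protocol.

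- **Endpoint.** The secondary outcomes table has "Time to first occurrence of a composite macrovasucular endpoint comprising" four components: "new diagnosis of lower extremity arterial disease (LEAD"), new or progressing foot ulcers, PAD-related surgical procedures, and coronary revascularisation. The window is "Time Frame: From baseline to 3 years of FU".
- **How LEAD is diagnosed.** The treatment algorithm, under Peripheral artery disease/foot ulcer, gives two routes. "Patients with or without symptoms of intermittent claudicatio and ABI<0.9 are diagnosed with lower extremity artery disease (LEAD"). An ABI above 1.4 leads to a TBI, and "If TBI is abnormal, patients will be diagnosed with lower extremity artery disease (LEAD").
- **Who gets the algorithm.** Under Organization in the Cardio-Metabolic clinic: "When Patients are randomized to the intervention arm a decision-making algorithm in the REDCap-system will be activated".
- **When ABI is measured.** Examinations, item 4: "ABI will be assessed at the baseline visit and at the 3 year follow-up visit". The Baseline visit section describes it before randomisation and for all participants, and the Three-year follow-up visit section repeats the baseline evaluation in everyone.
- **Controls.** Examinations, item 3, tells controls with raised blood pressure to contact their general practitioner. No action is written for an abnormal ABI.
- **Eligibility.** PAD at entry requires claudication with a pathological ABI, vascular PAD surgery or ischaemic amputation. A low ABI without symptoms can therefore enter the trial undiagnosed.
- **Start of counting.** The section on interventions in the clinic says that endpoint assessment begins only once the CMC intervention is complete.

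**The concern.** Two participants can be randomised with the same low ABI and no earlier diagnosis. In CMC the algorithm requires a LEAD diagnosis. In the control arm nothing in the Protocol does, so the label depends on usual care or on the year-3 visit. When the label itself is the endpoint event, in an open-label trial, part of the comparison reflects how actively each arm looked for disease and not how often disease developed.

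The direction is not fixed. If a first diagnosis prompted by the baseline ABI counts as new, CMC collects early events that controls do not. If such diagnoses are set aside in CMC because the clinic recognised them at once, while the same disease in controls counts when found later, the bias favours CMC. The delayed start of endpoint assessment acts in the same direction as this second case: it is tied to completing the CMC intervention, has no counterpart for controls, and conflicts with a time frame that runs from baseline.

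**Working it through.** **No figure to reproduce.** The Protocol gives no event rate, prevalence or power for this composite. What follows is a sensitivity calculation on assumed inputs.

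**From the Protocol:** 2:1 allocation of 1500, so about 1000 CMC and 500 controls; a 3-year window. The hazard ratio of 0.85 borrows the 15% reduction anticipated for the primary endpoint.

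**Assumed:** true event rate in controls 5% per year; undiagnosed LEAD at baseline u = 5–20%; all prevalent CMC cases diagnosed within about 0.1 year; a fraction f of prevalent control cases counted, either 10–30% through usual care over 3 years or all at the year-3 visit.

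**True 3-year risks:**
- Controls: q0 = 1 − exp(−0.05 × 3) = 0.1393
- CMC: q1 = 1 − exp(−0.05 × 0.85 × 3) = 0.1197

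**Observed risks if baseline-prompted diagnoses count:**
- CMC: u + (1 − u) × q1
- Controls: q0 + (1 − q0) × u × f

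Example, u = 10%, f = 30%: CMC 0.10 + 0.90 × 0.1197 = 0.2077; controls 0.1393 + 0.8607 × 0.10 × 0.30 = 0.1651; risk ratio 1.26. About 1000 × 0.10 = 100 of the CMC events would be prevalent disease.

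| u | CMC risk | Control risk, f = 10% / 30% / 100% | Risk ratio | Simulated Cox HR, f = 10–30% |
|---|---|---|---|---|
| 5% | 16.4% | 14.4 / 15.2 / 18.2% | 1.14 / 1.08 / 0.90 | about 1.1–1.2 |
| 10% | 20.8% | 14.8 / 16.5 / 22.5% | 1.40 / 1.26 / 0.92 | about 1.3–1.5 |
| 15% | 25.2% | 15.2 / 17.8 / 26.8% | 1.65 / 1.41 / 0.94 | about 1.6–1.8 |
| 20% | 29.6% | 15.7 / 19.1 / 31.1% | 1.89 / 1.55 / 0.95 | about 1.8–2.2 |

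The hazard ratios come from 60 simulated trials per setting; repeat runs differed by up to about 0.1. When every control case is counted at year 3, the simulated hazard ratio is about 0.91–1.10 across these prevalences. It lies above the risk ratio because CMC events fall near day 0 and control events at year 3.

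**Opposite direction.** Take no true effect and u = 10%. If prevalent cases are set aside in CMC but all are counted in controls, the 3-year risks are 13.9% in CMC and 1 − 0.90 × 0.8607 = 22.5% in controls.

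**Neutral definition.** In a separate simulation with no true effect and a 3-year composite risk of 10–20%, removing prevalent disease from both arms (u = 0) gave hazard ratios of 0.99–1.01. In the same simulation, 5% undiagnosed LEAD with no control case ever counted gave 1.28–1.53, and a falsely significant harm in 54–75% of trials.

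**The case against.** The strongest reply is that new ordinarily means not present at baseline. The baseline ABI exists in both arms, so the reading can be applied evenly, and prevalent disease then causes no bias. This is a fair reading, and it is why a reader should not infer that prevalent disease necessarily becomes an early CMC event: no sentence says that a low baseline ABI is scored. What remains is that the text does not choose this reading. The component is worded as a diagnosis, not as an ABI result, and a first diagnosis made after randomisation also fits the words.

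A reader might also infer that controls cannot be diagnosed, or that TBI-based diagnoses can arise only in CMC. The Protocol does not support that. Control care may include the endocrinology outpatient clinic, TBI is done at that department, and all participants repeat ABI at year 3. The supportable statement is that such diagnoses are protocol-driven only in CMC. Counting control cases at year 3 brings cumulative risks closer together, but not event times.

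The delayed start of endpoint assessment could remove early CMC diagnoses. Taken literally it does, but in one arm only, so it replaces one asymmetry with another.

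Finally, event definitions are often left to an analysis plan. That could settle what new means, but it cannot recover TBI results never obtained in controls. The Protocol itself ties the event to a diagnostic step of the intervention.

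**Conclusion.** The point holds as a matter of arm-dependent ascertainment, not as a demonstrated reversal of effect. As written, the LEAD component can be ascertained differently in the two arms, and the direction depends on how new and the start of counting are applied.

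The size cannot be known from the Protocol. Under the assumptions above, a true hazard ratio of 0.85 would appear as about 0.91–1.10 if control cases are counted at year 3, and about 1.1–2.2 if 70–90% of them are never counted. It is tempting to conclude that a real benefit would be erased or reversed. That follows only in part of this range: 0.91 is attenuation, and the upper values need the universal year-3 ABI to be ignored for most controls.

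The problem concerns one of four components of one secondary composite; the primary endpoint is untouched. It should be corrected, because the data for an even-handed definition are already collected.

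**What to change.** In the secondary outcomes table:

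1. Define the LEAD component from the study ABI, identically in both arms. Participants with known PAD, or with a baseline ABI below 0.9 or above 1.4, are prevalent and not at risk for this component. New LEAD is an ABI below 0.9 at the year-3 study measurement.
2. State that diagnoses made only through the clinic algorithm, including TBI-based ones, do not count as endpoint events.
3. Report LEAD as a year-3 outcome. Keep PAD procedures (amputations included) and coronary revascularisation in the time-to-first composite. Retain foot ulcers as stated, ascertained the same way in both arms.
4. State that endpoint counting starts at randomisation in both arms, and reconcile the sentence on delayed endpoint assessment with the time frame from baseline.

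This changes the endpoint definition only and leaves the clinical handling of an abnormal ABI as it is. It needs one amendment and no new measurements of ABI.

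The costs are fewer LEAD events, no LEAD dates between visits, missing LEAD status for participants who die or do not attend at year 3 (the Discontinuation section treats non-attenders as lost for outcomes that require attendance), and some overlap with the separate ABI-change outcome.
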